## Abstract

**Background:**

Several studies have shown an association of cryptogenic stroke and embolism with patent foramen ovale (PFO), but the question how to prevent further events in such patients is unresolved. Options include antithrombotic treatment with warfarin or antiplatelet agents or surgical or endovascular closure of the PFO. The PC-Trial was set up to compare endovascular closure and best medical treatment for prevention of recurrent events.

**Methods:**

The PC-Trial is a randomized clinical trial comparing the efficacy of percutaneous closure of the PFO using the Amplatzer PFO occluder with best medical treatment in patients with cryptogenic embolism, i.e. mostly cryptogenic stroke. Warfarin for 6 months followed by antiplatelet agents is recommended as medical treatment. Randomization is stratified according to patients age (<45 versus ≥45 years), presence of atrial septal aneurysm (ASA yes or no) and number of embolic events before randomization (one versus more than one event). Primary endpoints are death, nonfatal stroke and peripheral embolism.

**Discussion:**

patients were randomized in 29 centers of Europe, Canada, and Australia. Randomization started February 2000. Enrollment of 414 patients was completed in February 2009. All patients will be followed-up longitudinally. Follow-up is maintained until the last enrolled patient is beyond 2.5 years of follow-up (expected in 2011).

**Trial Registration:**

Trial listed in ClinicalTrials.gov as NCT00166257 and sponsored by AGA Medical, Plymouth, MN, USA

## Introduction

The cause of ischemic stroke is considered cryptogenic in 35-40% of cases [1]. Paradoxical embolism can be the cause of systemic embolism under all circumstances provided there is a right to left shunt, but it is blamed for an embolic event typically only in the absence of a left-sided thromboembolic source. Hence, paradoxical embolism via a patent foramen ovale (PFO) is entertained in the differential diagnosis especially in young patients (<60 years old) [2]. The detection of thrombus in the venous system or right atrium is not to be considered a prerequisite as non-detectable small clots are the most common culprits. Since the direct detection of thrombus within a PFO is rare [3-6], the diagnosis of paradoxical embolism is usually presumptive. While there is currently no proof for a cause-effect relationship, several studies have confirmed a strong association between the presence of a PFO and the risk for paradoxical embolism or stroke [7-11]. A PFO with a coinciding atrial septal aneurysm (ASA), spontaneous or large right-to-left shunt, or multiple ischemic events potentiates the risk of recurrence. [12]. The presence of a PFO or ASA has currently no therapeutic consequence in otherwise healthy adults. In contrast, patients suffering a stroke or transient ischemic attack (TIA) in the presence of a PFO are to be considered for medical therapy to reduce the risk of a recurrent embolic event (secondary prevention). Patients with PFO and ASA are defined as 'high-risk' patients for recurrent events. A retrospective French multicenter study in such patients reported a yearly risk of 1.2% to sustain a recurrent stroke and of 3.4% to suffer a recurrent stroke or TIA despite medical treatment with antiplatelet drugs or oral anticoagulants in patients with PFO and cryptogenic stroke [13]. In the Lausanne study no differences in risk reduction were noted between different modes of anticoagulant therapy with respect to recurrent stroke and TIA [14]. The Quality Standards Subcommittee of the American Academy of Neurology recently published evidence-based guidelines for the management of patients with recurrent stroke, PFO, and ASA, after a critical review of the literature [15]. Their main conclusion was that PFO alone does not portend an increased risk of subsequent stroke or death in patients who have had a cryptogenic stroke and are treated medically [15]. There were insufficient data to draw conclusions about isolated ASA. The results regarding patients with the combination of PFO and ASA were somewhat inconsistent and did not allow drawing conclusions for this subset of patients.

Nonsurgical closure of PFO has become possible with the advent of implantable devices, and has long been demonstrated feasible and safe [16,17]. It represents an attractive treatment alternative to life-long antiplatelet therapy or oral anticoagulation in patients with PFO and paradoxical embolism.

The optimal treatment strategy of such symptomatic patients remains to be defined, although nonrandomized data suggest an advantage of percutaneous PFO closure over medical treatment [18,19]. Thus the true therapeutic efficacy of percutaneous PFO closure as an adjunct or alternative to medical treatment needs to be ascertained by randomized studies.

## Methods

### Rationale for the present study

While there is good evidence for the association between the presence of PFO and the risk for paradoxical embolism, a cause-effect relationship has not been conclusively established. Furthermore there are no publications of prospective, randomized studies comparing the efficacy of different treatment modalities in patients with PFO and paradoxical embolism including percutaneous device closure.

The purpose of the present study is to compare the efficacy of percutaneous PFO closure using the *Amplatzer PFO Occluder *(AGA Medical Corporation, Plymouth, MN, USA), with medical treatment in patients with presumed paradoxical embolism in a prospective, randomized trial.

### Null-hypothesis to be rejected

Percutaneous device closure of PFO with the *Amplatzer PFO Occluder *is of equal efficacy compared with medical treatment in the prevention of recurrent stroke and/or TIA in patients with paradoxical embolism.

### Design overview

This is a multicenter, multinational, randomized, clinical trial comparing the efficacy of percutaneous PFO closure using the *Amplatzer PFO Occluder *with best medical treatment in patients with PFO and paradoxical embolism. The organization and scientific conduct of the study is supervised by a Steering Committee. A Data and Safety Monitoring Board is responsible for safety and ethical aspects. A Clinical Events Committee review and adjudicate all reported adverse events and endpoints. Study monitoring and data management is carried out by a contract research organization.

### Study endpoints

The primary objective of this study is to investigate whether percutaneous PFO closure using the *Amplatzer PFO Occluder *is superior compared to best medical treatment in the prevention of symptomatic, recurrent thromboembolism. The following combined primary endpoint will therefore be assessed at each scheduled follow-up visit: death, nonfatal stroke, and peripheral embolism.

Patients who experience a primary endpoint event during the study period no longer have to continue the treatment allocated at the time of randomization. The management of patients who suffer a primary endpoint event will be left to the discretion of the responsible physician. Crossover from medical treatment to PFO device closure or vice versa from PFO device closure to additional antithrombotic treatment will be allowed in case of a primary endpoint event. However, all patients will continue to be followed up for further events after an initial primary endpoint according to the study protocol for the total duration of this study. Appendix 1 details the primary and secondary endpoints.

### Patient selection criteria

Patients with PFO and presumed paradoxical embolism who meet all inclusion criteria but no exclusion criteria of Appendices 2 and 3 are offered to participate in this study. After obtaining a written informed consent, patients were randomised in 29 centers of Europe, Canada, and Australia. Randomization started February 2000. Enrolment of 414 patients was completed in February 2009. All patients will be followed-up longitudinally as outlined in Table 1. Follow-up is maintained until the last enrolled patient is beyond 2.5 years of follow-up (expected in 2011).

**Table 1 T1:** Timetable of prospective investigations during the study.

	Baseline	Hospitalization	6 months	1 year	2 years	3 years	4 years	5 years
History	x		x	x	x	x	x	x
Listing of antithrombotic medications	x	x	x	x	x	x	x	x
Laboratory survey	x							
12 lead ECG	x	x	x	x	x	x	x	x
Holter ECG	x							
TEE*	x	X (TTE or TEE)	x					(x)
CT/MR or angiography of region of interest (brain or periphery)	x							
Carotid Doppler	x							
Employment status	x		x	x	x	x	x	x
Quality of life	x		x	x	x	x	x	x
Stroke outcome classification (NIH SS, Barthel index, Modified Rankin scale)	x	x	x	x	x	x	x	x
Procedural complications		x						
Primary endpoints			x	x	x	x	x	x
Secondary endpoints			x	x	x	x	x	x

*TEE examination after 6 months and possibly yearly thereafter until complete closure of the PFO has been documented. A TEE at 5 years of follow-up or termination of the study is optimal; a TTE is acceptable immediately following device closure.

### Treatment assignment

Randomization was done by a research contract organization (InterCorNet, Zurich, Switzerland) through computer-generated block randomisation forms for each participating centre. Patients were stratified according to age (≥45 vs. <45 years) and presence or absence of ASA. Percutaneous PFO closure was scheduled as soon as possible following randomization. Implantation occurred according to standard techniques by experienced operators familiar with the Amplatzer PFO Occluder.

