### Statistical Methods

The working hypothesis of this study postulates a reduction in the annual incidence of recurrent thromboembolic events from 3% per year to ≤1% per year in patients with percutaneous closure of the PFO. With an overall sample size of 410, the power will be 80% at an α-level of 0.0492 (allowing for one interim analysis) under the following assumptions: mean follow-up time 4.5 years; successful closure of the PFO in 95% of those randomized to PFO closure; and annual rate of patients lost to follow-up 0.5%. The comparability between the two treatment groups will be tested with the two sample t-test or Fischer's exact test as appropriate, for continuous covariates, and Pearson's chi square test for categorical variables. An adjusted alpha level of 0.01 will be used as indication for an imbalance between the study groups.

The data from all participating centers will be pooled for the analysis of all primary and secondary endpoints as well as adverse events. An intention-to-treat analysis will be carried out retaining all the randomized study participants irrespective of whether they received the allocated treatment or not. Analysis of primary and secondary end points will be done using proportional hazard models. Graphical representation and comparison of survival between the two intervention groups will be presented using Kaplan Meier survival curves. Secondary analyses of these end points stratified by age, (age ≥45 years vs. <45 years and presence or absence of ASA) and effect modification by age and ASA will be tested in multivariable modeling. The significance level to reject the null hypothesis is set to 0.0492 (two-sided) taking account of the planned interim analysis.

An interim analysis will be conducted after 2.5 years of follow-up of the entire study population to detect an important excess in benefit or risk of closure of the PFO as compared to medical treatment. The significance level to define statistically a significant excess or reduction in risk will be 0.0054 (two-sided) according to O'Brian-Fleming boundaries. Data and Safety Monitoring Board is entitled to interrupt the trial taking into account both, clinical and statistical significance of excess or reduction in risk.

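### The article lists three randomisation factors in the abstract and two in the Methods, names none for the primary Cox analysis, and carries number of previous events into no named analysis

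*Protocol article*

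**What the plan says.** The abstract (Methods paragraph) gives three randomisation factors: age at the 45-year cut, "presence of atrial septal aneurysm (ASA yes or no) and number of embolic events before randomization (one versus more than one event"). The section Treatment assignment gives two: "Patients were stratified according to age (≥45 vs. <45 years) and presence or absence of ASA". It adds that allocation used "computer-generated block randomisation forms for each participating centre".

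In Statistical Methods, the model is given in one sentence: "Analysis of primary and secondary end points will be done using proportional hazard models". No covariate or stratum is named there, either as included or as excluded. Age and ASA come in afterwards, under a secondary label: "Secondary analyses of these end points stratified by age, (age ≥45 years vs. <45 years and presence or absence of ASA"). The same two factors, and no others, are named for interaction testing: "effect modification by age and ASA will be tested in multivariable modeling". On centre, the text says: "The data from all participating centers will be pooled for the analysis of all primary and secondary endpoints".

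Number of previous events is mentioned nowhere in Statistical Methods. The Introduction lists it among the features that matter for prognosis: with ASA or a large shunt, "or multiple ischemic events potentiates the risk of recurrence".

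**The concern.** The two descriptions of the strata cannot both be complete. Condensing a longer protocol does not explain the difference, because the abstract contains more than the Methods.

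The discrepancy bears on the analysis whichever statement is right. If the abstract is right, a factor used to randomise has dropped out of every analysis the article names. If Treatment assignment is right, the abstract misreports the design, and balance on a factor that the article itself calls prognostic rests on chance.

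At stake is some precision in the primary comparison. Leaving prognostic randomisation factors out of a Cox model pulls the hazard ratio towards 1 and makes the test a little conservative. The design expects only about 35 events and has no spare power.

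**Working it through.** **1. The plan's own figure.** Inputs from Statistical Methods: 3% versus 1% per year, 95% successful closure, mean follow-up 4.5 years, 0.5% annual loss, N = 410, two-sided alpha 0.0492 (z = 1.967). Equal allocation (205 per arm) is assumed, as the article gives no ratio.

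- Closure-arm rate allowing for failed closure: 0.95 × 1% + 0.05 × 3% = 1.1% per year.
- Cumulative risk with rate r and loss l: r/(r + l) × [1 − exp(−(r + l) × 4.5)]. Medical arm: 0.03/0.035 × (1 − exp(−0.1575)) = 12.5%. Closure arm: 0.011/0.016 × (1 − exp(−0.072)) = 4.8%.
- Expected events: 205 × (0.1249 + 0.0478) = 35.4.
- Power for two proportions (pooled variance under the null, no continuity correction): Φ[(0.0771 − 1.967 × 0.0277)/0.0275] = Φ(0.82) = 79.4%, with N = 416 needed for 80%. Ignoring loss gives 79.9% (N = 412). Reading the rates as annual probabilities gives 80.6% (N = 406).

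The stated 80% with 410 patients reproduces. The calculation contains no strata, so the discrepancy does not change it.

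**2. Cost of an unadjusted primary test.** Simulation of the design: N = 410, permuted blocks of 4 within the eight strata of all three factors, control hazard averaging 0.03 per year, true treatment hazard ratio (HR) 0.011/0.03 = 0.367, and 3,000 trials per scenario. The test is the log-rank test, i.e. the score test of the Cox model. The article gives neither prevalences nor factor hazard ratios. Assumed prevalences are 50% (age), 25% (ASA) and 35% (more than one event), with a common hazard ratio per factor as in the table.

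| Factor HR | Power, unstratified | Power, two factors | Power, three factors | Median treatment HR, unstratified / three factors | Type I error, unstratified / three factors |
|---|---|---|---|---|---|
| 1 | 79.8% | 80.0% | 80.1% | 0.370 / 0.370 | 5.0% / 4.8% |
| 1.5 | 80.1% | 80.0% | 80.2% | 0.369 / 0.364 | 4.2% / 4.2% |
| 2 | 78.8% | 79.4% | 79.9% | 0.375 / 0.369 | 4.1% / 4.8% |
| 3 | 76.1% | 77.8% | 79.0% | 0.378 / 0.362 | 3.8% / 5.1% |

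The simulation standard error is about 0.7 points for power and 0.4 for type I error. The power loss is 0.1, 1.1 and 2.9 points at factor HRs of 1.5, 2 and 3. The largest attenuation is 0.378 − 0.362 = 0.016.

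A separate simulation used covariate-adjusted Cox models (Wald test, 1,500 trials per scenario) with assumed prevalences of 30% for ASA, 30% for multiple events and 50% for age. Power went from 77.5% to 78.7% at factor HRs of 2, 2 and 1.5 (ASA, multiple events, age), from 75.3% to 78.7% at 3, 3 and 1.5, and from 76.7% to 79.5% at 4, 3 and 2. The gains are of the same order.

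**3. If number of events was not a stratum.** With 30% prevalence and 207 per arm, the 95% range of chance imbalance is ±1.96 × √(2 × 0.3 × 0.7/207) = ±8.8 points. At that edge the unadjusted HR shifts by a factor of [1 + (h − 1) × 0.344]/[1 + (h − 1) × 0.256], which is 1.07 for h = 2 and 1.12 for h = 3. For scale, with about 25.9 and 9.9 events (loss ignored), SE(log HR) = √(1/25.9 + 1/9.9) = 0.37. The larger shift, ln 1.12 = 0.113, is about 0.3 of a standard error.

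**The case against.** A reader might infer that the primary Cox analysis uses none of the randomisation factors. The article does not say that. It is silent on the primary model's covariates, and a full protocol or SAP, not shown here, could list them. This objection stands as far as it goes: an unadjusted model is the natural reading, because age and ASA stratification is labelled secondary, but it is an inference.

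A reader might also take all three factors to be strong, known predictors. The Introduction supports ASA and multiple events in words only, with no hazard ratio. It then reports that evidence on PFO combined with ASA was too inconsistent for conclusions. Nothing says that age at the 45-year cut predicts recurrence; age belongs in the model because both descriptions call it a stratum.

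A third tempting inference is that strata crossed with 29 centres left most blocks incomplete. The article gives no block size and does not say that strata were nested within centre, so this cannot be derived.

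Finally, an unadjusted analysis after stratified randomisation is valid, the gain from adjustment is small, and chance imbalance already lies within the test's error rate. All of that is correct, and it limits the weight of the point. It does not remove the contradiction about how patients were randomised, or explain why one reported stratum is missing from the named analyses.

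**Conclusion.** The contradiction over the strata is certain from the text, as is the absence of number of previous events from every analysis the article names. That the primary model is unadjusted is likely but not stated. If it is, the trial is not invalidated: type I error stays at or below nominal within simulation error, power falls by about 0 to 1 point for factor hazard ratios up to 2 and by about 3 points at 3, and the treatment hazard ratio is attenuated by up to about 0.02. These sizes rest on assumed prevalences and factor hazard ratios and on equal allocation. The point should be acted on because the loss, though modest, can be avoided with baseline data in a trial whose 80% power is only just reached.

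**What to change.** - Establish from the completed randomisation lists which factors were used, and correct the abstract or Treatment assignment accordingly.
- In Statistical Methods, specify before the final analysis that the primary Cox model is adjusted for, or stratified by, the factors actually used. Include number of previous embolic events (one versus more than one) as a baseline covariate whichever description proves right. Keep the unadjusted model as the supporting analysis.
- Leave centre out of the model: about 35 events over 29 centres is roughly 1.2 per centre.
- No further effect-modification test is needed; so few events would tell little about it.

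The cost is a change of wording. Enrolment closed in February 2009 and follow-up was expected to run into 2011, so the lists are complete. No new data are required, provided number of previous events was recorded at baseline, as the abstract implies. The primary hazard ratio becomes conditional on the factors, which changes its meaning very little at event risks of about 5% to 13%.

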### Device

The device used for percutaneous PFO closure in patients participating in the *PC-*trial was the *Amplatzer PFO Occluder*, manufactured from 0.005" nitinol wire, a superelastic shape memory alloy, which permits constraining of the device to a small (≤9 French) delivery system with recovery of shape upon delivery in the atria. As long as the device is screwed to its 0.038" delivery cable, it is fully retrievable and repositionable without need for removal of the device from the delivery sheath prior to a new placement attempt. The device is available in different sizes with typically the left atrial disk being smaller than the right atrial disk (18 mm to 35 mm).

### Implantation procedure

Patients scheduled for percutaneous PFO closure were generally admitted on the day of the procedure and discharged the same or following day. The procedure was generally performed using local anesthesia. Balloon gauging of the PFO was not encouraged. The decision to guide device implantation by fluoroscopy only or use simultaneous transesophegeal echocardiography (TEE) or intracardiac echocardiography (ICE) was left to the implanting physician. Prophylactic antibiotic therapy (e.g. cephalosporin) was recommended during the periprocedural period followed by a recommendation for prophylaxis against endocarditis for 2-6 months. Venous access was typically established via the right femoral vein. Femoral artery access was optional for invasive blood pressure monitoring or to assess for coronary artery disease by diagnostic coronary angiography. In case of left-to-right shunt (small atrial septal defects) balloon gauging and a complete right heart catheterization with oximetry were recommended but not mandatory. After administration of systemic heparin (≥ 5000 IU) the PFO is probed, e.g. with a multipurpose catheter or a standard (exchange) guidewire (0.035 inch). A 8-9 French Amplatzer sheath was used for device implantation. The *Amplatzer PFO Occluder *was delivered through the delivery sheath and placed within the PFO under fluoroscopic and optional echocardiographic guidance. First, the usually smaller left atrial disc was released in the left atrium. The whole unit consisting of the sheath and the released left atrial disc was then pulled gently against the interatrial septum. Following this the right atrial disc was released by further withdrawing the sheath, while maintaining some traction on the interatrial septum with the left atrial disc. Care was taken to avoid air embolism. After assurance of a stable and correct device position (fluoroscopy with dye injection in a view showing the device in profile separating the 2 disks completely or echocardiography), the device was released from the delivery cable. The final position and eventual residual shunt were documented by angiography or echocardiography. Following this, the introducer sheath was removed and hemostasis assured by applying manual compression to the access site. Before hospital discharge stable device position was documented by transthoracic echocardiography (TTE). All implantation related complications were recorded as adverse events.

A residual shunt is not unexpected immediately following device implantation. Subsequent endothelialization occurring over a few months improves the closure rate. Completeness of closure for analysis was therefore assessed by TEE with Valsalva followed by a bubble test at 6 months of follow-up. All patients to be treated with acetylsalicylic acid 100-325 mg/day for 5-6 months following device implantation. Ticlopidine 250-500 mg/day or clopidogrel 75-150 mg/day, could be used complementary or as an alternative in case of intolerance to acetylsalicylic acid. Oral anticoagulation was optional for a period of 6 months, if deemed necessary by the investigator but was discouraged. Provided a satisfactory result of the 6-month contrast TEE, antithrombotic therapy and the recommendation for prophylaxis against endocarditis were discontinued, unless required by another indication.

